#### Treatment as usual

2.4.1

This study aims to evaluate whether adding TH to a standardized regimen of treatment as usual (TAU) provides additional benefit. To independently assess the additive effect of TH as an adjunctive therapy, the control group receives two weeks of TAU during the trial period. All TAU is provided according to the hospital’s standard clinical pathways. TAU comprises treatment and usual care. The treatment consists of antidepressant medication, supplemented by physical therapy, psychotherapy, and rehabilitation training. The usual care includes admission orientation, health education on symptoms, consequences and treatment options for depression and NSSI as well as the importance of treatment adherence, medication guidance, discharge planning, and psychological support.

During the study period, the provision of TAU is at the discretion of the attending physician. Participants are not restricted from receiving other treatments or care beyond the designated protocol. To address potential heterogeneity in TAU, the following TAU components will be systematically recorded for all participants throughout the trial: antidepressant medication, including drug name, daily dose, and any dose adjustments; physical therapy, including type, frequency, and duration; psychotherapy, including modality, number of sessions, and duration; and rehabilitation training, including type and frequency. If a participant’s symptoms worsen and require additional treatment, all related details are fully documented in the case report form. These data will be incorporated into the statistical analysis to control for potential confounding effects.

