Prior to the intervention, baseline characteristics and baseline outcome measures will be compared between the two groups to assess the balance achieved by randomization. Normally distributed continuous variables will be presented as mean ± standard deviation (SD) and compared using the independent samples t-tests. Non-normally distributed continuous variables will be presented as median and interquartile range (Median, IQR) and compared using the Mann-Whitney U test. Categorical variables will be presented as frequency and percentage (n, %) and analyzed using Chi-square test or Fisher’s exact test.

Analysis of Covariance (ANCOVA) will be used to assess the intervention effects. The post-intervention (T_1_) score will serve as the dependent variable, with the group assignment as a fixed factor and the corresponding baseline (T_0_) score included as a covariate in the model. Analysis of Covariance (ANCOVA) will be used to assess the intervention effects. The post-intervention (T_1_) score will serve as the dependent variable, with the group assignment as a fixed factor and the corresponding baseline (T_0_) score included as a covariate in the model. The primary outcome is a single endpoint and is exempt from multiplicity adjustment. To control for inflation of Type I error due to multiple comparisons across the five secondary outcomes, the Benjamini-Hochberg False Discovery Rate (FDR) correction will be applied to the following outcomes as a family: depressive symptoms measured by HAMD-17, alexithymia measured by TAS-20, self-efficacy measured by GSES, sleep quality measured by PSQI, and loneliness measured by UCLA-LS. A Generalized Linear Mixed Model (GLMM) will be used for a secondary analysis of the primary outcome. A Generalized Linear Mixed Model (GLMM) will be used for a secondary analysis of the primary outcome.

A reduction of ≥30% in the NSSI level score from baseline is prespecified as the minimal clinically important difference (MCID). Participants who achieve this reduction are defined as responders, and the responder rate will be compared between groups using the chi-square test or Fisher’s exact test. For all outcomes, effect sizes (Cohen’s d) with 95% confidence intervals will be reported.

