To account for potential confounding arising from heterogeneity in TAU, the following variables derived from the systematically recorded TAU components will be prespecified as covariates and entered simultaneously into the primary ANCOVA model: number of psychotherapy sessions received as a continuous variable, antidepressant dose as a continuous variable, and receipt of physical therapy, defined as rTMS or ECT and coded as a binary variable. Rehabilitation training will be examined descriptively by group; if a between-group difference at *P* < 0.10 is detected, this variable will be added as an additional covariate in sensitivity analyses. When repeating the primary analysis on the LOCF-imputed FAS and the PPS, all prespecified TAU covariates will be retained in the model to verify the robustness of the adjusted treatment effect.

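### The primary ANCOVA adjusts for usual treatment received after randomisation, so it may not estimate the effect of adding therapeutic horticulture

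*Protocol article*

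**What the plan says.** Section 2.9 first describes the ANCOVA for the outcomes: the T1 score is the dependent variable, "with the group assignment as a fixed factor and the corresponding baseline (T_0_) score included as a covariate in the model". The last paragraph of that section then names three TAU variables, "prespecified as covariates and entered simultaneously into the primary ANCOVA model: number of psychotherapy sessions received as a continuous variable", together with "antidepressant dose as a continuous variable, and receipt of physical therapy, defined as rTMS or ECT and coded as a binary variable". The reason given is possible confounding from varying TAU. The same covariates are to be kept when the primary analysis is repeated on the LOCF-imputed full analysis set and on the per-protocol set. Rehabilitation training is added in sensitivity analyses only, if the arms differ at P < 0.10.

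Section 2.4.1 shows where the variables come from. "TAU components will be systematically recorded for all participants throughout the trial", among them "antidepressant medication, including drug name, daily dose, and any dose adjustments". It also says that "the provision of TAU is at the discretion of the attending physician". On worsening it says: "If a participant’s symptoms worsen and require additional treatment, all related details are fully documented in the case report form". It then adds: "These data will be incorporated into the statistical analysis to control for potential confounding effects".

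Section 2.4.1 gives the aim as the additive effect of TH on top of TAU, and section 2.9 commits to the intention-to-treat principle.

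**The concern.** The trial asks what adding TH does to NSSI severity when TAU runs its normal course. That is the total effect of allocation, and a comparison that uses only information fixed before allocation estimates it. A variable that arises after allocation can be a consequence of it. If TH improves patients, physicians may escalate medication or physical therapy less. If TH takes up time, other therapy may be used less. Holding such a variable constant removes whatever part of the effect runs through it. Where unmeasured severity drives both TAU and the outcome, it also mixes severity into the treatment contrast.

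Confounding is not the right reason for this adjustment. TAU differences present before allocation are balanced in expectation by randomisation, and the confidence interval covers chance imbalance. TAU differences that appear later may be effects of TH. At stake is the one confirmatory estimate of the trial.

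**Working it through.** **1. Timing of the covariates.** Section 2.3 places randomisation after consent and baseline assessment. Against that:

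| Covariate (section 2.9) | Timing |
|---|---|
| Psychotherapy sessions | After randomisation: counted as received |
| rTMS or ECT | After randomisation: coded as receipt |
| Antidepressant dose | Not stated whether baseline, mean or final; the record in section 2.4.1 runs through the trial and includes adjustments, so on-trial dose is the natural reading |

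**2. Can allocation affect them?** TAU is discretionary and can be added to on worsening (section 2.4.1). Section 2.3 names only outcome assessors and data analysts as blinded. Even a blinded physician would respond to a patient who improves or worsens, so the route exists. Whether it operates is not known.

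**3. The plan's own figure.** Inputs from section 2.8: difference 13, SD 17.59, two-sided alpha 0.05, power 80%, attrition 10%.

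n = 2 × (1.960 + 0.842)² × 17.59² / 13² = 28.74, rounded up to 29 per group. 29 / 0.9 = 32.2, rounded up to 33 per group, 66 in total. The stated figure reproduces, and it does not depend on the TAU covariates.

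**4. Size of the bias under assumptions.** One standardised on-trial TAU variable M stands in for the three covariates:

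- M = a·g + u·U + noise, with variance 1 within arm. Here g is the arm, U is unmeasured severity, a is the effect of TH on M in SD units, and u is the correlation of M with severity.
- Y = (Δ − a·b)·g + b·M + 8·U + noise, with total SD about 17.59. Here b is points per SD of M and Δ is the total effect of allocation.

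The values of a, b, u and the 8 points per SD of severity are assumptions, not figures from the article. The baseline score was given no predictive value.

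Without M in the model, the coefficient of g is Δ. With M in the model, E[U | g, M] = u·(M − a·g), so the coefficient of g becomes

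Δ − a·(b + 8u).

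The bias is −a·(b + 8u). It is zero when a = 0, that is, when TH leaves TAU unchanged. Example: a = −0.5, b = 5, u = 0.5 gives −13 + 0.5 × (5 + 4) = −8.5.

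Simulation: 66 patients, 4,000 runs per row. Power and rejection are two-sided at 0.05.

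| a | b | u | Formula, Δ = −13 | Simulated, adjusted | Power, adjusted v baseline-only | Δ = 0: adjusted estimate, rejection rate |
|---|---|---|---|---|---|---|
| 0 | 0 | 0.5 | −13.0 | −12.9 | 0.84 v 0.83 | 0.0, 0.05 |
| −0.5 | 0 | 0 | −13.0 | −13.0 | 0.81 v 0.84 | 0.0, 0.06 |
| −0.3 | 0 | 0.5 | −11.8 | −11.7 | 0.76 v 0.84 | +1.2, 0.06 |
| −0.5 | 0 | 0.5 | −11.0 | −11.0 | 0.69 v 0.84 | +2.0, 0.07 |
| 0.5 | −5 | 0 | −10.5 | −10.3 | 0.65 v 0.82 | +2.4, 0.08 |
| −0.5 | 5 | 0.5 | −8.5 | −8.4 | 0.57 v 0.83 | +4.5, 0.20 |
| −0.8 | 0 | 0.7 | −8.5 | −8.4 | 0.46 v 0.83 | +4.5, 0.16 |
| −0.5 | −5 | 0.5 | −13.5 | −13.5 | 0.83 v 0.83 | −0.5, 0.05 |

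The baseline-only model averaged about −13 when Δ = −13, and rejected in about 5% of runs when Δ = 0. Higher scores are worse, so the positive estimates at Δ = 0 count against TH. The last row shows that the sign can also go the other way.

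**The case against.** The strongest reply is that the bias is only a possibility. Section 2.4.2 intends the same two-week TAU in both arms, no passage says that TH displaces psychotherapy, and the check itself finds no material bias when TH leaves TAU alone. This stands as a limit on the claim. It does not rescue the plan, because section 2.4.1 lets TAU vary and records it for that reason. If TAU did stay the same in both arms, the adjustment would not be needed to remove bias.

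Four stronger readings are tempting, but the article does not support them:

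- **Two rival primary models, with a choice left open.** Section 2.9 gives the general ANCOVA and then adds covariates to it, so it can be read as one prespecified model. The wording should be aligned, but no free choice is shown.
- **No analysis is free of TAU adjustment.** The responder comparison has no covariates, and none are named for the GLMM. Only the LOCF and per-protocol repeats are said to keep the TAU terms. Still, a dichotomised outcome and a model with unstated covariates do not replace the plain ANCOVA on the score.
- **Milligrams of different drugs are pooled.** The article does not state a scale for dose, and drug name is recorded, so conversion is possible.
- **The rehabilitation P < 0.10 rule alters the primary model.** It applies to sensitivity analyses only, though it also conditions on treatment given after allocation.

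Nor is this a detail left to a fuller plan: the article itself names the covariates and places them in the primary model.

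**Conclusion.** The point holds in conditional form. The primary model conditions on treatment received after randomisation that allocation may affect, and the stated reason, confounding, does not justify this in a randomised comparison. It would go too far to say that the adjusted estimate must be wrong: the bias depends on TH changing TAU, and on TAU being linked to the outcome directly or through severity. Under the assumed scenarios the estimate ran from about −8.4 to −13.5 for a true −13, power fell to as low as 0.46 against 0.83, and type I error reached 0.20 with no true effect. These figures show a range under chosen inputs and do not predict this trial. Neither size nor direction can be settled from the article. Because the LOCF and per-protocol repeats carry the same terms, their agreement with the primary result would be no reassurance on this point. It should be corrected before the data are analysed.

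**What to change.** - Make the primary model the T1 ASHS level score on group plus T0 score, as the general ANCOVA description in section 2.9 already has it. Limit any further covariates to values fixed before randomisation.
- Use the same model in the LOCF and per-protocol repeats.
- Report TAU received during the trial descriptively by arm.
- Label any model that adjusts for on-trial TAU as exploratory, including the rehabilitation-training rule. If dose enters such a model, state its time point and put it on a common scale across drugs.
- Align the wording of section 2.4.1 and the two places in section 2.9, and drop confounding as the reason for adjustment.

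The cost is wording only. The data are already to be collected, and the sample size stays at 29 per group before attrition and 66 in total.

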Current primary interventions for NSSI in adolescents with MDD include pharmacological, physical, and psychological treatments. Pharmacotherapy is widely used but requires consideration of side effects, dependency, and potential increased suicide risk in some adolescents (11). Common physical interventions include repetitive transcranial magnetic stimulation (rTMS) and (Electroconvulsive Therapy, ECT). While preliminary research suggests rTMS may be a promising method, its mechanisms are not fully understood, and robust clinical evidence specifically for NSSI is lacking (12). Some studies have also confirmed that ECT can significantly reduce NSSI in adolescents (13). However, this therapy may be accompanied by a series of adverse effects, such as headache and nausea, and therefore requires cautious use (14). Additionally, some patients and their families are reluctant to accept this treatment, and its efficacy for NSSI remains a subject of debate.

The 2022 UK National Institute for Health and Care Excellence (NICE) guideline on self-harm assessment, management, and relapse prevention emphasizes that interventions for NSSI in adolescents with depression require a comprehensive assessment and treatment of comorbidities and psychosocial factors (15). Evidence-based psychological interventions recommended for NSSI in adolescents with depression include cognitive behavioral therapy (CBT) (16), dialectical behavior therapy (DBT) (17), and acceptance and commitment therapy (ACT) (18) and other interventions. While these therapies show efficacy, they are often constrained by high time and financial costs, specialized requirements, and limited service availability (19). Furthermore, given adolescent developmental characteristics, long-term, single-modality treatments may exacerbate negative emotions, reduce treatment acceptance and adherence, and induce resistance, thereby diminishing therapeutic effects (20). Therefore, exploring effective, integrated, psychologically appealing interventions with minimal side effects is of paramount importance.

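### Antidepressant dose enters the primary ANCOVA as one continuous term with no common scale across drugs, time point or multi-drug rule, so it cannot be relied on to adjust for treatment intensity

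*Protocol article*

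**What the plan says.** Section 2.9 (Statistical methods) gives the purpose of the adjustment as "To account for potential confounding arising from heterogeneity in TAU". It names three variables that "will be prespecified as covariates and entered simultaneously into the primary ANCOVA model". One is a count of psychotherapy sessions. The other two are "antidepressant dose as a continuous variable, and receipt of physical therapy, defined as rTMS or ECT and coded as a binary variable". The same covariates are kept when the primary analysis is repeated on the LOCF-imputed data and on the per-protocol set.

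Section 2.4.1 (Treatment as usual) describes where the dose variable comes from. For drug treatment the record holds "antidepressant medication, including drug name, daily dose, and any dose adjustments". The drug is not fixed: "the provision of TAU is at the discretion of the attending physician", and "Participants are not restricted from receiving other treatments or care beyond the designated protocol".

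Section 2.9 says that the covariates are derived from these records but gives no derivation for dose. Section 4 (Ethics and dissemination) says that the analysis plan is presented in this article and is also available through the registry.

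**The concern.** A single slope per unit of dose is coherent only if a unit means the same for every drug. The plan expects several drugs, since it records drug name separately from daily dose and adjusts because usual treatment will vary. If the covariate is the recorded daily dose, two participants treated with equal intensity on different drugs can have very different values. Two participants with the same value can be treated with very different intensity.

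The variable also has no unique value for anyone whose dose is changed, who switches drug or who takes two antidepressants within the two weeks. Two analysts could then get different primary estimates from the same data. That part needs no assumption about which drugs are used.

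At stake is whether the primary model delivers the adjustment it promises. The LOCF and per-protocol repeats carry the same covariate, so they would not expose the problem.

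**Working it through.** **Inputs from section 2.8.** Difference 13, SD 17.59, two-sided alpha 0.05, power 80%, 10% attrition. The plan's figure reproduces: 2 × (1.960 + 0.842)² × 17.59² / 13² = 28.74, so 29 per group, and 29 / 0.9 = 32.2, so 33 per group. The sample size is not in question. It supplies the SD and group size used below.

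**Assumptions, because the documents name no drugs, doses or mix.** Two drugs with typical doses 1 and k; a proportion p of participants on the larger-amount drug; within-drug coefficient of variation c; no relation between drug and relative dose. Relative dose r is the dose divided by that drug's typical dose.

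**Formulas.** Mean μ = (1 − p) + pk. Between-drug variance B = p(1 − p)(k − 1)². Within-drug variance W = c²[(1 − p) + pk²]. Between-drug share = B / (B + W). R² of unconverted dose with relative dose = (μc²)² / [c²(B + W)].

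**One case in full**, k = 5, p = 0.5, c = 0.4: μ = 3, B = 0.25 × 16 = 4, W = 0.16 × 13 = 2.08. Share = 4 / 6.08 = 66%. R² = 0.48² / (0.16 × 6.08) = 0.24.

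**Range over p = 0.10 to 0.50 and c = 0.25 to 0.5:**

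| Ratio of typical doses | Between-drug share | R² with relative dose |
|---|---|---|
| 1 | 0% | 1.00 |
| 1.5 | 7-38% | 0.60-0.91 |
| 2 | 22-63% | 0.33-0.73 |
| 3 | 44-80% | 0.15-0.44 |
| 5 | 55-87% | 0.07-0.31 |
| 10 | 62-91% | 0.03-0.23 |

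**When one drug dominates.** The share falls to zero if everyone takes the same drug, but it matters which drug dominates. At k = 5 and c = 0.4 with 90% on the larger-amount drug, μ = 4.6, B = 0.09 × 16 = 1.44 and W = 0.16 × 22.6 = 3.62, so the share is 28%. With 10% on the larger-amount drug, B is again 1.44 but W = 0.16 × 3.4 = 0.54, and the share is 73%.

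**Effect on the treatment estimate.** Simulation of 4,000 trials per setting, 33 per arm, true difference −13, p = 0.5, c = 0.4, dose unaffected by allocation, no other covariates. Entries are the SD of the treatment estimate:

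| Dose-outcome correlation | k | No dose term | Unconverted dose | Common scale |
|---|---|---|---|---|
| 0.3 | 2 | 4.31 | 4.21 | 4.13 |
| 0.3 | 5 | 4.30 | 4.29 | 4.13 |
| 0.3 | 10 | 4.34 | 4.32 | 4.16 |
| 0.5 | 2 | 4.35 | 4.03 | 3.74 |
| 0.5 | 5 | 4.31 | 4.21 | 3.78 |
| 0.5 | 10 | 4.38 | 4.31 | 3.88 |

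The mean estimate lies between −12.9 and −13.1 in every setting. Theory agrees: with no dose term the SD is 17.59 × √(2/33) = 4.33, and a common-scale term with correlation 0.5 gives 4.33 × √(1 − 0.25) = 3.75.

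**The case against.** The plan nowhere says that dose is used unconverted. It says that the variables are derived from the records, and both drug name and daily dose are recorded, so a conversion is possible. An article may also leave such detail to a fuller document. This is fair as far as it goes. However, the article does fix the form of the variable for the primary model, names no conversion, and describes itself as presenting the analysis plan. The registry copy is not shown, so a definition there cannot be excluded.

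A reader might infer that the covariate must mainly encode the drug and cannot adjust for dose at all. The documents do not support that. At a 1.5-fold difference the unconverted dose still carries 60-91% of the information in relative dose, and at 2- to 3-fold the picture is mixed. Only at about 5-fold or more does drug identity account for most of the variance throughout the tested range.

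A reader might also infer a biased treatment effect. If dose is unaffected by allocation, randomisation protects the comparison and the simulation shows no bias. In that simulation unconverted dose did no worse than leaving dose out, so the harm is a benefit forgone.

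Two further inferences do not stand. The yes/no code for rTMS or ECT does not share this fault: an indicator of receipt has no unit, and pooling the two is a defensible economy with 66 participants. That participants on large-amount drugs would distort the fit as leverage points has not been shown by any calculation.

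Finally, which drug a participant takes is itself part of the variation in usual treatment. That is so, but one linear term in dose is a poor way to represent it, and a drug or class term would do so openly.

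**Conclusion.** The point holds as an inexpensive improvement to the primary model. The dose covariate lacks a common scale, a time point and a rule for several drugs, so it cannot be relied on to adjust for treatment intensity and is not uniquely computable for participants whose treatment changes.

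The size depends on a drug mix that the documents do not give. At 5- to 10-fold differences in typical dose and an equal split, almost all the gain from adjustment is lost. The SD of the treatment estimate is about 11% larger than on a common scale if the dose-outcome correlation is 0.5 (4.21 / 3.78 and 4.31 / 3.88), and about 4% larger if it is 0.3 (4.29 / 4.13 and 4.32 / 4.16). With similar typical doses, or everyone on one drug, little or nothing is lost. The consequence is lost precision and weak correction of chance imbalance. The absence of bias rests on dose being unaffected by allocation, which a value taken before allocation would secure.

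**What to change.** In section 2.9, replace the dose covariate with a defined one: each participant's daily dose at T0, before the allocation envelope is opened, divided by a reference daily dose for that drug and summed over concurrent antidepressants. Take all reference doses from one published source, named before unblinding. Use the same variable in the LOCF and per-protocol repeats. If no scale can be agreed, drop the term and report drug and dose by arm descriptively.

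The cost is a change of wording and a short conversion table. Drug name and daily dose are already recorded, and treatment, visits and sample size do not change. There are two downsides. Equivalence tables are approximate. A T0 value does not capture dose changes during the two weeks, so these should be reported descriptively by arm.
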